
### Fear Acquisition and Generalization Paradigm

2.7

Participants undergo the fear acquisition and generalization paradigm used in earlier assessments (Schiele, Reinhard, et al. 2016), using neutral female faces as conditioned stimuli (03F_NE_C, 10F_NE_C, NimStim Face Stimulus Set; Tottenham et al. 2009). CS+ is paired with a fearful face and aversive scream (International Affective Digitized Sounds, IADS, FemScream2, No. 276; Bradley and Lang 1999), while CS‐ remains unpaired. The experiment includes three phases: pre‐acquisition (unreinforced CS+ and CS‐), acquisition (CS+ reinforced on most trials, while CS‐ remains unpaired), and generalization (CS+, CS‐, and four morphed generalization stimuli, GS1–GS4, with partial CS+ reinforcement). Stimuli are presented with randomized order and intertrial intervals. After each phase, participants rate stimuli on arousal, valence, and US expectancy. An overview of the fear acquisition and generalization paradigm is shown in Figure 3. Compared to earlier assessments, fewer generalization trials are included (see Table 3), with analyses focusing on this first block.

#### Avoidance

2.7.1

After the generalization paradigm, participants complete a costly avoidance task to dimensionally measure safety behavior, adapted from Wong and Pittig (2022). A reward threshold for hearing the scream is first determined with yes/no monetary offers. Based on this threshold, participants rate their willingness to avoid the scream (0%–100%) for each CS and GS, where higher avoidance decreases both scream probability and the potential reward. After each rating, US expectancy is assessed. Importantly, CS‐ and GS trials are never reinforced, and all rewards are hypothetical, which effectively modulates avoidance behavior (Pittig and Dehler 2019; Pittig and Scherbaum 2020). Finally, participants identify which image was paired with the scream in prior assessments and rate their confidence to control for memory effects. The whole experiment lasts approximately 45 min.

#### Physiological Recordings and Data Reduction

2.7.2

Heart rate and skin conductance responses are recorded at 1000 Hz using Brainproducts hardware and software. Heart rate variability (HRV) is assessed before and after the paradigm via ECG electrodes, while participants watch a neutral video. RR intervals are processed and analyzed in Kubios HRV software to derive markers for autonomic nervous system activity. Skin conductance response (SCR) is measured on the left hand, range‐corrected, log‐transformed, and averaged per stimulus, with participants showing mean responses < 0.02 μS classified as non‐responders and excluded.

### Bioprobes

2.8

#### Blood Cell Analysis

2.8.1

Blood samples are collected after the experimental paradigm to analyze blood cell composition and routine indices. The total blood volume collected is 18.1 mL, divided as follows: 9 mL EDTA for (epi)genetics and blood cell counts, 7.5 mL serum for metabolomics and hormone analyses, and 1.6 mL EDTA specifically for a differential blood count. Serum is centrifuged 20 min after collection at 2500g for 15 min at 4°C. Samples are stored at −80°C for later analysis. All participants had previously been genotyped at the genome‐wide association study (GWAS) level using high‐throughput genotyping arrays (1st wave PsychChip and 2nd wave GSA 3.0).

#### HPA‐System

2.8.2

On the endocrine level, cortisol is measured from four saliva samples collected at home in the morning after awakening, using a provided test kit and instructions. Ideally, sampling occurs on the study day or a typical working day close to it: the first sample at awakening, followed by three more at 15‐min intervals over 45 min. Participants are asked to avoid food, drink, or physical activity, and are encouraged to remain in bed engaging only in low‐arousal activities such as reading. After collection, participants store the samples in a freezer until bringing them to the study site. If needed, the study team arranges sample pickup within the Würzburg area (for recommendations see Stalder et al. 2016, 2022). Additionally, two saliva cortisol samples are collected pre‐ and post‐fear generalization to assess task‐related stress responses.

*Note: A priori genotyping:* Probability of selected genes being involved in anxiety endophenotypes, assessed using rapid low‐throughput and high‐throughput genotyping methods. *Post‐hoc genotyping:* Validation of genetic variants based on prior hypotheses (e.g., animal studies or prior research findings). *Whole Genome Sequencing (WGS):* Comprehensive analysis of all genetic variations. *Genome‐Wide Association Studies (GWAS):* Broad screening for variant‐trait associations. *Gene × environment (× coping) analyses:* Stepwise multivariate regression analyses linking genetics, environment, and coping, extended by epigenetic data (e.g., DNAm). *Blood cell analysis:* Blood composition (e.g., red cell distribution width) and routine indices as indicators of psychopathology. *Polygenic risk scores:* Analysis to estimate the cumulative genetic risk for anxiety‐related traits. *Neuroimaging backbone module:* Brain morphology (structural MRI), functional connectivity (resting‐state fMRI), and data analysis at categorical (anxiety disorders), dimensional (anxiety sensitivity), and epigenetic levels. *HPA‐System:* Salivary cortisol measurements (e.g., after awakening and in response to a fear generalization paradigm) to evaluate stress responses.

### Statistics

2.9

Main analyses address our three major research questions: (i) stability of fear acquisition and generalization processes, (ii) prediction of the developed anxiety‐related psychopathology, and (iii) the relationship of fear acquisition and generalization processes and saliva cortisol levels. Analyses may be adjusted for new methods or data quality (e.g., missing data, distributions).

#### Stability of Fear Generalization Processes

2.9.1

To examine the stability of fear generalization, we will calculate established indicators and firstly adapt the approach outlined by Cooper et al. (2023). Linear mixed models with a fixed effect of stimulus for the acquisition phase and generalization will test differential fear conditioning. Furthermore, building on the approach by Cooper et al. (2023), additional models will be applied to examine mean‐level changes in fear responses over time. These models will include a random intercept for participants and random slopes for timepoint, as well as fixed effects of stimulus, phase (acquisition only), timepoint (T1, [T2,] FU), and their interactions. To investigate individual patterns of fear generalization, additional mixed‐effects models will be fitted to examine the effect of timepoint on the Linear Deviation Score (LDS). Age and the Age × Timepoint interaction will be included in all models to account for variability in the interval between the initial assessment and follow‐up, as well as cohort‐related age differences. As age effects are not central to the present research question, they will not be considered further. A more fine‐grained modeling of temporal variability will be implemented in the prediction analyses (see below *Prediction of anxiety symptomatology*).

Next, we aim to replicate the variance component analysis based on the principles of generalization theory to examine how variance is distributed across different levels of the model and to evaluate the relative contributions of individual differences, stimuli, and sessions to the observed effects (Cooper et al. 2023).

Further, we will assess intraindividual stability (i.e., within‐subject stability of response patterns) and change (i.e., within‐subject reliability of change) using the coefficients *R*
_IRS_ and *R*
_C_. *R*
_IRS_, as used by Torrents‐Rodas et al. (2014), quantifies the proportion of within‐person variance in stimuli responses that remains stable across time. This measure is well‐suited to capture stability of generalization patterns, as it isolates the consistency of individual differences in response patterns over repeated sessions. To complement this, we will also calculate the *R*
_C_ coefficient (Cooper et al. 2023), which measures the reliability of change in responses across individuals between timepoints. It quantifies how much non‐stable variance in responses reflects changes over time. Larger *R*
_C_ suggest reliable tracking of systematic changes in response patterns across sessions.

We will also calculate Intraclass Correlation Coefficients (ICCs) to assess response consistency. Beyond Cooper et al. (2023)'s stimulus‐specific ICCs for acquisition and generalization phases, we will include three additional indices (Stegmann et al. 2019): ICCs based on the Linear Deviation Score, the Mean Response across all stimuli, and CS‐Differentiation, enabling interpretation of individual response patterns during generalization.

To investigate age‐related trajectories of fear generalization, we will apply likelihood‐based linear mixed models in the combined child, adolescent and adult samples depending on resulted estimates (Mallinckrod et al. 2008). This approach allows joint analysis of all timepoints based on a multivariate model useful to analyse longitudinal continuous outcomes.

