### Test‐Retest Reliability

1.2

Testing whether fear generalization alterations predispose to ANX assumes they are trait‐like, requiring test‐retest reliability (Torrents‐Rodas et al. 2014). For fear acquisition, evidence is mixed (for a summary see Klingelhöfer‐Jens et al. 2022, supplement): early work showed moderate‐to‐strong SCR reliability (Fredrikson et al. 1993), but recent studies report modest and measure‐dependent stability (Klingelhöfer‐Jens et al. 2022). For fear generalization, Torrents‐Rodas et al. (2014) calculated generalizability coefficients (G coefficients) to estimate the proportion of individual variation in responses to CSs and GSs, finding stable individual differences across 8 months in startle, SCRs, and threat expectancy (*R*
_IRS_ = 0.17–0.34) (Torrents‐Rodas et al. 2014). SCRs showed fair reliability in fear acquisition and generalization, while threat expectancy was less consistent over 1–2 weeks (Cooper et al. 2023). Overall, fear generalization shows short‐ and mid‐term reliability, though subjective ratings appear less stable, and long‐term data are lacking.

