### Recruitment

2.2

In this study, all Würzburg adults from two prior Z02 cohorts who completed the fear learning paradigm, as well as children and adolescents who participated in both earlier assessments and consented to recontact, are invited. This yields two timepoints for adults (T1 > T2) and three for youths (T1, T2 > T3; see Figure 1). Earlier assessments included extensive psychometric evaluations of anxiety symptoms, a fear conditioning and generalization paradigm, and genetic phenotyping.

Re‐recruitment is expected at ≥ 40% for adults and ≥ 50% for adolescents. Exclusion criteria include acute psychosis, suicidality, pregnancy, and illicit drug use (verified by urine toxicology). Unlike initial enrollments (Table 1), participants with psychopathologic traits are intentionally included to track longitudinal development.

**TABLE 1 mpr70094-tbl-0001:** Overview and eligibility criteria of the initial and follow up sample.

	A‐T1/1 and A‐T1/2	C‐T1 and C‐T2	Follow‐up
Inclusion criteria	Age between 18 and 50 years Caucasian background Right‐handedness Fluency in German	Age between — 8 and 12 years (C‐T1) or — 12 and 16 years (C‐T2) Caucasian background Right‐handedness Fluency in German	Participants of adult cohort A‐T1/1 and A‐T1/2 that performed the paradigm Participants of the child and adolescent cohort C‐T1 and C‐T2 that took part in both assessments
Exclusion criteria	Major clinical disorders Pregnancy Severe medical conditions Ongoing medication intake Use of illegal drugs as assessed by urine toxicology More than 14 glasses alcohol per week More than 20 cigarettes per day More than 4 cups caffeine per day	Severe somatic conditions Intake of psychoactive medication Low intelligence (IQ < 85)	Pregnancy Use of illegal drugs as assessed by urine toxicology

Participants are first contacted in writing (email or letter), followed by a telephone call to provide more details and confirm eligibility. Oral informed consent is obtained, and interested participants are invited to complete an additional CAR measurement. For those unable to visit Würzburg, online options are available for clinical interviews and psychometric assessments.

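### The mean-level change models in section 2.9.1 name no participant × stimulus random effect, so their stimulus and stimulus × timepoint standard errors are wrong if personal response patterns are stable

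*Protocol article*

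**What the plan says.** Section 2.9.1 describes the models for mean-level change thus: "These models will include a random intercept for participants and random slopes for timepoint, as well as fixed effects of stimulus". The list of fixed effects goes on to phase (acquisition only) and "timepoint (T1, [T2,] FU), and their interactions", so stimulus × timepoint is a tested term. The section mentions no random stimulus effect, structured residual covariance or robust standard error for these models.

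The same section then plans R_IRS, which "quantifies the proportion of within‐person variance in stimuli responses that remains stable across time" and which "isolates the consistency of individual differences in response patterns over repeated sessions". Section 1.2 gives R_IRS values of 0.17–0.34 from an earlier study, summarised as "finding stable individual differences across 8 months in startle, SCRs, and threat expectancy".

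On the data structure, section 2.2 states: "This yields two timepoints for adults (T1 > T2) and three for youths". Ratings are collected once per stimulus at the end of each phase (section 2.7), and skin conductance is averaged by stimulus (section 2.7.2). For generalization this means one value per participant, stimulus and occasion.

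**The concern.** The stated random part lets participants differ in overall level and in level at each occasion. It does not let them differ in how they respond to one stimulus relative to another. That difference is the quantity R_IRS is meant to capture, and the evidence the article cites puts it above zero. One analysis therefore sets to zero a component that the next analysis in the section exists to estimate.

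If the component is present, the omission has two opposite effects in the generalization models. A stable personal pattern recurs at every wave, so waves are less independent for stimulus contrasts than the model assumes, and tests of stimulus are too liberal. The same pattern cancels when waves are compared, but the model still counts it as noise, so tests of stimulus × timepoint are too conservative. The second effect bears on whether the average fear gradient changed between assessments, which these models are there to examine.

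**Working it through.** The article gives no power or alpha calculation for these models, so there is no figure of its own to reproduce.

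**Inputs**
- R = 0.17 to 0.34 (section 1.2, cited 8-month study). R = 0.05 is added as an assumed low value, because no figure exists for 3–12 years.
- T = 2 waves for adults and 3 for youths (section 2.2).
- One value per participant, stimulus and occasion in generalization (sections 2.7 and 2.7.2).
- Two-sided 5% level: assumed, as none is stated.

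**Model.** Response = fixed effects + participant + participant × timepoint + participant × stimulus (PS) + residual (e), in a balanced design. R = var(PS) / [var(PS) + var(e)], with the denominator scaled to 1. Without PS, the fitted residual variance is 1 and is treated as independent across waves.

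**Formulas**
- Stimulus contrast averaged over T waves: true SE / model SE = √(1 + (T − 1)R).
- Stimulus × timepoint contrast: PS cancels, so true SE / model SE = √(1 − R).
- Actual level = 2[1 − Φ(1.96 / ratio)].
- Interaction power, when a correct analysis has 80%: Φ(2.80 − 1.96 / ratio).

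**Results, one value per cell**

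| Test | R | SE ratio | Actual level |
|---|---|---|---|
| Stimulus, T = 2 | 0.05 | √1.05 = 1.025 | 5.6% |
| Stimulus, T = 2 | 0.17 | √1.17 = 1.082 | 7.0% |
| Stimulus, T = 2 | 0.34 | √1.34 = 1.158 | 9.0% |
| Stimulus, T = 3 | 0.17 | √1.34 = 1.158 | 9.0% |
| Stimulus, T = 3 | 0.34 | √1.68 = 1.296 | 13.1% |
| Stimulus × timepoint | 0.05 | √0.95 = 0.975 | 4.4% |
| Stimulus × timepoint | 0.17 | √0.83 = 0.911 | 3.1% |
| Stimulus × timepoint | 0.34 | √0.66 = 0.812 | 1.6% |

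Interaction power: at R = 0.17, Φ(2.80 − 2.15) = 74%; at R = 0.34, Φ(2.80 − 2.41) = 65%.

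**Checks.** The SE ratios do not depend on sample size. Simulation with 6 stimuli, 8,000 replicates per setting and the follow-up numbers in the Discussion (357 adults, 226 children) gave, for R = 0.17 and 0.34:
- stimulus: 7.1% and 9.1% (T = 2), 9.1% and 13.6% (T = 3);
- stimulus × timepoint: 3.1% and 1.8% (T = 2), 2.8% and 1.5% (T = 3).

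One simulated data set (357 participants, T = 2, R = 0.34) was fitted by REML with and without the PS term. Adding it moved the stimulus SE from 0.0351 to 0.0410 (×1.17) and the interaction SE from 0.0703 to 0.0561 (×0.80). The timepoint main-effect SE stayed at 0.0459.

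**Acquisition.** Phase gives several records per participant-stimulus-timepoint cell, so the formulas above do not apply. Take J = 2 or 3 records per cell, two stimuli and T = 2. With R = 0.17–0.34 and no participant × stimulus × timepoint variance, the true stimulus SE is 1.27–1.77 times the model SE. Let that three-way variance range over an assumed 0–0.2 of the total: the interaction ratio then runs from 0.86 to 1.20, so the error can have either sign.

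**The case against.** **The omission is inferred.** A list of what a model will include need not be exhaustive, the article condenses a fuller plan, and the Statistics section reserves a general right to adjust analyses. This carries some weight. But the random terms are named explicitly, and a general reservation does not correct a named structure.

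**The R range is borrowed.** It comes from another study over 8 months, and section 1.2 itself says long-term data are lacking. This stands: 0.17–0.34 is a conditional input and not a property of this study. At R = 0.05 the problem is negligible.

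**Stability is judged elsewhere.** A reader might infer that the conservative interaction test pushes the study towards a trait-like conclusion. The document does not support that. The Discussion does not tie trait-like inference to a non-significant mean-level interaction. The stability evidence comes mainly from the variance components, R_IRS, R_C and the ICCs, none of which uses these standard errors. Section 2.9.1 also plans a separate model for the effect of timepoint on the Linear Deviation Score. That score is one value per person and occasion, so a stable pattern is absorbed by a participant intercept. It does not cover every stimulus contrast, so it softens the point without removing it.

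**The stimulus main effect matters less here.** Differential conditioning is tested in separate models whose random part is not described, and no stated conclusion is shown to rest on the stimulus null in the change models. That also stands.

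**Trial-level data.** A reader might extend the argument to trial-by-trial skin conductance and expect an inflated interaction test. The article describes averaging by stimulus, so that case is not part of this point.

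**Conclusion.** The point holds, with limited reach. As specified, the mean-level change models give wrong standard errors for stimulus and stimulus × timepoint whenever stable person-specific stimulus responses exist; the errors vanish only at R = 0. In generalization the size is modest to moderate if R_IRS over 3–12 years resembles the cited 8-month values, and small if R is near 0.05. This rests on one value per cell, a balanced design, an assumed 5% level, and the named random terms being the complete list. For acquisition, only further understatement of the stimulus standard error is established; no single direction can be claimed for the interaction. The timepoint main effect and the planned reliability coefficients are unaffected, so the study's answer on trait-like stability is not put in doubt by this point alone.

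**What to change.** Add a participant × stimulus random effect, e.g. (1|id:stimulus), to the acquisition and generalization change models. Where a cell holds several records, as in acquisition with phase, also add (1|id:stimulus:timepoint). With a single value per cell this last term cannot be separated from the residual and is not needed. The planned variance-component analysis already covers individuals, stimuli and sessions, so the change brings the two analyses into line. The cost is one or two model terms and slightly longer fitting; no new data are required.

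### With one value per person, stimulus and session, R_C cannot show reliable change in generalization patterns; it should be read as reliability of individual change in overall responding

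*Protocol article*

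**What the plan says.** Section 2.9.1 of the protocol article plans a variance component analysis "to evaluate the relative contributions of individual differences, stimuli, and sessions to the observed effects". Two coefficients follow from it.

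- **R_IRS** is for stability of the profile over stimuli. It is chosen "as it isolates the consistency of individual differences in response patterns over repeated sessions". In this paragraph, then, a response pattern means the profile over CS+, CS- and the GSs.
- **R_C** is the complement, "which measures the reliability of change in responses across individuals between timepoints". It is said to quantify how much non-stable "variance in responses reflects changes over time". No formula is given. The paragraph ends by stating that larger values "suggest reliable tracking of systematic changes in response patterns across sessions".

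The data that feed these coefficients are described elsewhere. Section 2.7: "After each phase, participants rate stimuli on arousal, valence, and US expectancy". Section 2.7.2: SCR is range-corrected, log-transformed "and averaged per stimulus". Follow-up has one generalization block, "with analyses focusing on this first block". Table 3 gives two acquisition blocks at every wave.

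**The concern.** Within one paragraph the subject moves from change in responses to change in response patterns. These are different variance components. Change in a person's overall level between sessions is person x session. Change in the shape of the profile is person x stimulus x session. With one value per cell, the second has no error term of its own.

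Stability is the first of the three main research questions (section 2.9), and the Discussion builds its trait-versus-state reading on whether responding is stable or changes. R_C is the coefficient meant to tell real change from noise. If it is read as the article says, people who differ in how much they habituate would be reported as showing systematic change in generalization patterns. Section 3.1 itself names habituation as a risk. A genuine reshaping of gradients could pass as noise.

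**Working it through.** The plan gives no R_C value, so there is no figure to reproduce. The check concerns what the coefficient can identify.

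**Inputs from the article.** Six stimuli in generalization (k = 6), one value per cell, two sessions for adults and three for youths, and the facets person, stimulus and session. All variances below are assumptions, because the article gives none.

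**Step 1: identifiability.** Write v_pt for person x session, v_pst for person x stimulus x session and v_e for error. In a crossed design with one value per cell:

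- E[MS_pt] = (v_pst + v_e) + k·v_pt
- E[MS_res] = v_pst + v_e

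Only the sum v_pst + v_e can be estimated. This holds for any coefficient built from this decomposition.

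**Step 2: assumed form.** The usual generalizability form, which fits the article's wording, is

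R_C = v_pt / [v_pt + (v_pst + v_e)/k].

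With v_pt = 0.20 and v_pst + v_e = 0.40:

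- k = 6: 0.20/(0.20 + 0.40/6) = 0.20/0.267 = 0.75
- k = 2: 0.20/(0.20 + 0.40/2) = 0.50

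Both values are the same whether v_pst is 0, 0.20 or 0.40. The k = 2 line applies to acquisition only if it too has one value per cell.

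**Step 3: behaviour under different kinds of change** (k = 6). Simulation with 315 adults (40% of 526 + 262 = 788), two sessions and 300 replicates agreed with the formula. The last column omits the division by k.

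| Scenario | Calculation | R_C | Without /k |
|---|---|---|---|
| Noise only, v_e = 1.0 | 0/(0 + 1.0/6) | 0 | 0 |
| Nearly pure pattern change, v_pst = 0.9, v_e = 0.1 | 0/(0 + 1.0/6) | 0 | 0 |
| Level change only, v_pt = 0.3, v_e = 0.5 | 0.3/(0.3 + 0.5/6) | 0.78 | 0.37 |
| Same, plus v_pst = 0.5 | 0.3/(0.3 + 1.0/6) | 0.64 | 0.23 |
| Same level change, v_e = 1.0, no pattern change | 0.3/(0.3 + 1.0/6) | 0.64 | 0.23 |
| Same level change, v_pst = 1.5, v_e = 0.5 | 0.3/(0.3 + 2.0/6) | 0.47 | 0.13 |

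Pattern change and noise give identical results.

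**Step 4: pattern change that moves the stimulus mean.** Let the four GSs alone shift by a person- and session-specific amount with variance 0.5, and let v_e = 0.5.

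- Residual: 0.5 + 0.5 × (4 × (1/3)² + 2 × (2/3)²)/5 = 0.633
- MS_pt: 6 × 0.5 × (4/6)² + 0.5 = 1.833
- Estimated v_pt: (1.833 − 0.633)/6 = 0.20
- R_C: 0.20/(0.20 + 0.633/6) = 0.65

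This pattern change does raise R_C, but as apparent level change.

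**Step 5: what a replicate would add.** In a simulation with six trials per cell and true v_pst = 0.50, the residual of the cell means was 0.988 and the within-cell variance divided by six was 0.503. The difference, 0.988 − 0.503 = 0.485, recovers v_pst.

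**The case against.** The other side has several good points.

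- **The formula is inferred.** The article prints none, and the cited source is not available here. This stands for the sizes in Steps 2 to 4. It does not affect Step 1.
- **One value per cell is read from a condensed data-reduction sentence.** The full plan might keep trials or blocks. For acquisition this has weight, since two blocks could act as partial replicates. For generalization, the text describes one rating per stimulus after the phase, an SCR average per stimulus and a single block.
- **Patterns are already covered.** Section 2.9.1 models the effect of timepoint on the LDS and adds ICCs for LDS, Mean Response and CS-Differentiation. A pure level change should show in Mean Response and not in LDS. This limits the damage considerably, but it does not make the R_C sentence true.
- **The definition of R_C is compatible with a level reading.** That is so. Only the closing sentence goes further.

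A reader might also draw two stronger conclusions, and neither is supported. The first is that general habituation would inflate R_C. A drop shared by all participants is a session main effect. It adds nothing to person x session variance, and the timepoint fixed effect in the planned models captures it. Only habituation that differs between people raises R_C. The second is that R_C would point the wrong way, falling whenever patterns truly change. Step 4 shows that a selective rise in GS responding raises it. The coefficient is non-specific; it is not reversed.

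**Conclusion.** The interpretation is wrong as written for the generalization block. On the data described, R_C cannot distinguish change in level from change in pattern. Pattern change that cancels over stimuli is counted as error, and pattern change that shifts the stimulus mean appears as level change. In the illustration a value of 0.75 is compatible with any share of true pattern change in the residual, from none to all.

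The confounding rests only on one value per cell and the three named facets. The reading of R_C as reliability of between-person differences in overall change rests further on the assumed person x session form, and the numbers rest on assumed variances. The position for acquisition is less clear. R_C may still be computed; what needs to change is the claim attached to it.

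**What to change.** **Wording.** In section 2.9.1, interpret R_C as the reliability of individual differences in change of overall responding. Base statements about pattern change on the LDS and CS-Differentiation analyses already planned. With one value per session these show average change and stability of a pattern index; for ratings they do not by themselves establish that individual change in pattern is reliable, so that claim should not be made.

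**Optional, for SCR.** Where trial-level values exist for all waves, form odd- and even-trial means per stimulus and add them as a replicate facet. Person x stimulus x session can then be estimated apart from error. Two conditions apply:

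- The trials must be a matched first-block set. Table 3 lists six trials each for GS2 to GS4 at follow-up but 12 each in the earlier waves. The earlier listing adds to 6 + 6 + 6 + 12 + 12 + 12 = 54 against a stated 36, so the true counts need confirming first.
- Half of the CS+ trials are reinforced (3 of 6), so the halves should be balanced on reinforcement.

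**Cost.** No new measurements at follow-up. The claim for ratings becomes narrower. SCR gains one variance component, with noisier half-means.
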